## Abstract

**Background:**

Although some interventions have been shown to improve adherence to medication for diabetes, results are not consistent. We have developed a theory-based intervention which we will evaluate in a well characterised population to test efficacy and guide future intervention development and trial design.

**Methods and Design:**

The SAMS (Supported Adherence to Medication Study) trial is a primary care based multi-centre randomised controlled trial among 200 patients with type 2 diabetes and an HbA1c of 7.5% or above. It is designed to evaluate the efficacy of a two-component motivational intervention based on the Theory of Planned Behaviour and volitional action planning to support medication adherence compared with standard care. The intervention is delivered by practice nurses. Nurses were trained using a workshop approach with role play and supervised using assessment of tape-recorded consultations. The trial has a two parallel groups design with an unbalanced three-to-two individual randomisation eight weeks after recruitment with twelve week follow-up. The primary outcome is medication adherence measured using an electronic medication monitor over 12 weeks and expressed as the difference between intervention and control in mean percentage of days on which the correct number of medication doses is taken. Subgroup analyses will explore impact of number of medications taken, age, HbA1c, and self-reported adherence at baseline on outcomes. The study also measures the effect of dispensing medication to trial participants packaged in the electronic medication-monitoring device compared with conventional medication packaging. This will be achieved through one-to-one randomisation at recruitment to these conditions with assessment of the difference between groups in self-report of medication adherence and change in mean HbA1c from baseline to eight weeks. Anonymised demographic data are collected on non-respondents. Central randomisation is carried out independently of trial co-ordination and practices using minimisation to adjust for selected confounders.

**Discussion:**

The SAMS intervention and trial design address weaknesses of previous research by recruitment from a well-characterised population, definition of a feasible theory based intervention to support medication taking and careful measurement to estimate and interpret efficacy. The results will inform practice and the design of a cost-effectiveness trial [ISRCTN30522359].

## Background

Diabetes is a major public health problem. The number of people with diabetes is estimated to reach 330 million by 2030 [1]. There is a high clinical and economic burden from the disease [2]: people with diabetes have a two-to-four fold increased risk of cardiovascular disease compared to the general population and increased incidence of retinopathy, peripheral nerve damage and renal problems.

Evidence supports the use of multiple medications to control blood glucose and cardiovascular risk among patients with type 2 diabetes [3], and, this may lead to prescriptions of eight or more medications a day. Up to half of this medication may not be taken as prescribed [4,5], with adherence to medication falling as dosage frequency rises [6]. Failure to take medication has important consequences. It not only reduces efficacy of the treatment, but wastes healthcare resources in prescribed pills not taken, extra consultations, referrals, investigations and hospital admissions [7,8]. The availability of an effective intervention to support patients with type 2 diabetes in taking their medication regularly would make a major contribution to human health.

A variety of interventions to support adherence to medication have been tested for efficacy [9], and their clinical application assessed [10]. Although some interventions are effective in improving adherence, the results are inconsistent. These studies have used complex packages of care, targeting multiple self-care activities and therefore limiting identification of factors that lead to and might modify non-adherence. Approaches to supporting behaviour change are now informed by evidence about the psychological determinants of behaviour, and techniques to alter them, and there is potential to apply these techniques in the field of medication adherence [11,12].

Adherence to medication can be defined in many ways. Our definition is the extent to which medicines are taken regularly as prescribed. We argue that to understand the determinants of adherence better and optimise the impact of different intervention components upon them, we need to design interventions based on clear conceptual frameworks. We also need to test whether targeting determinants of medication adherence (e.g., patient's beliefs) results in greater levels of adherence [11,13].

People may not take their medication because of ambivalence about pros and cons of adherence (intentional lapse). Others, who intend to take their medications regularly, may still forget to do so (non-intentional lapse). Intentional and non-intentional lapses in adherence have been identified as two important elements contributing to overall non-adherence [14]. Drawing on psychological theory and evidence [15,16], we have developed approaches to address these two elements: to increase patients' motivation to take their tablets regularly by targeting underlying beliefs; and to help patients define specific action plans to facilitate the translation of intentions into action and habit formation. The two components can be defined as motivational – targeting the cognitive determinants of intention – and volitional – defining action plans to implement the target behaviour [15].

The motivational component of the intervention is based on the Theory of Planned Behaviour (TPB) [16]. This theory specifies beliefs which may be targeted to strengthen intention. In particular techniques include reinforcement of positive beliefs and problem solving approaches to negative beliefs. The theory's constructs account for 35 to 50% of variance in intention and 26 to 35% of variance in behaviour [17]. This illustrates a gap between intention and behaviour. The use of action planning, also called implementation intentions[15], is a promising approach to bridge this gap. A range of studies has demonstrated that explicit consideration of the circumstances under which a behaviour will be enacted (action plans), promotes clinically important change in specific health related behaviours including consumption of vitamin C tablets, attendance for cervical cytology screening and breast self-examination [18].

In clinical trials evaluating medication taking, adherence in the control group is often high. This may be because patients willing to participate in trials are likely to be adherent, because self-report measures may overestimate true adherence, or because more objective measurement focuses attention, on this target behaviour [7,10]. To interpret the effects of interventions better, future trials need to characterise the population from which participants have been recruited by collecting data about non-responders, encouraging respondents who do not wish to take part in the trial to complete baseline questionnaires, and investigating the effect of measurement itself on adherence and clinical risk.

In previous pilot work we have developed measures and interventions [19] using the approach defined by the Medical Research Council Framework for development of interventions for evaluation in randomised trials [20,21]. We therefore intend to estimate the efficacy of support for medication adherence on medication taking behaviour using motivational and action planning techniques; and estimate the effect of monitoring medication-taking itself on self-reported adherence and glycaemic control in a randomised trial. The trial addresses important limitations in the literature by recruitment from a well-characterised population, definition of a feasible intervention to support medication taking, and careful measurement to estimate and interpret efficacy.

## Methods/Design

### Trial design

This parallel group trial has two sequential randomisations. The main randomisation takes place eight weeks after recruitment, is unbalanced and compares a two-component intervention addressing motivation and action planning with a control intervention in which patients only take part in data collection (Figure 1). Unbalanced randomisation is used to maximise experience with the intervention across a range of patients with follow up at twenty weeks. The measurement effect randomisation, which takes place at the baseline recruitment visit, is balanced and assesses the effect of dispensing medication in a container that records opening compared with dispensing medication in standard packaging: with follow up at eight weeks.

**Figure 1 F1:**
[figure not shown]
Flow of participants through study.

### Ethical approval

The London, multi-centre research ethics committee has reviewed and approved the protocol (06/MRE02/3).

### Setting

Recruitment of patients is from general practices in Oxfordshire, Milton Keynes, Suffolk, Essex and Huntingdonshire.

### Patients

Patients are eligible for inclusion in the trial if diagnosed aged 18 years or above with type 2 diabetes of at least three months duration, able to give informed consent, currently taking any oral glucose-lowering agent and with a HbA1c ≥ 7.5%. Those approached are deemed by their general practitioner able to complete a consent form, independent in medication taking, and appropriate for tight glycaemic control.

### Intervention

After an eight week period of initial observation, patients are allocated to either an intervention visit to support medication adherence, or to a control visit at which their current medication regimen is recorded.

The intervention was developed and piloted after a detailed study to identify beliefs held about diabetes [19]. The intervention visit is delivered by the practice nurse. In the first, motivational component of the intervention, the nurse elicits the patient's beliefs relevant to their intention to take medication regularly as prescribed based on the TPB. Nurses use scripts to guide the order and phrasing of questions that elicit individual beliefs about benefits and harms, views of important others and factors that may facilitate or inhibit taking medication regularly as prescribed. Positive beliefs are reinforced with provision of tailored information and problem solving is applied in relation to negative beliefs [16]. In the second, action planning component, the nurse asks the patient to write down the exact circumstances under which they will take their medication (using an "if.then" formulation to elicit where, when and how this will occur) [15]. In the control visit, delivered by the practice nurses, none of the above techniques are applied.

### Intervention fidelity

Initial training is provided over one day for the practice nurses delivering the intervention, using a workshop approach with role-play led by a psychologist and intervention facilitators involved in quality assurance of intervention delivery. It includes explanation of the rationale for the intervention, use of a detailed manual providing information about the theoretical base and operationalisation of the different components, how to use the intervention to establish agreement with the prescription plan, and use of a 'script' to promote fidelity of intervention delivery. Assessment of audiotapes of intervention sessions is conducted to assess fidelity of delivery using standardised forms. Subsequently, coaching and feedback is provided to the nurses to optimise intervention delivery. Possible sources of bias in intervention delivery are addressed with the practice nurses throughout training and ongoing support. These include the need to avoid (i) delivering the intervention to control group patients, (ii) discussing the intervention techniques with other members of the primary care team and (iii) using intervention techniques not specified in the script.

### Measurement effect

At the baseline visit patients are randomised to be dispensed their metformin tablets in a container with a lid that records the occurrence and timing of opening (TrackCap, Aardex, Zurich, Switzerland), or to continue taking their medication in standard packaging as before the trial. If participants are not taking metformin, another of their usual oral hypoglycaemic medication is dispensed in the electronic medication-monitoring device.

### Randomisation

Randomisation of patients to assess intervention and baseline measurement effects is carried out independently of trial co-ordination and intervention by the trial statistician. A partial minimisation procedure is used to dynamically adjust randomisation probabilities to balance the baseline stratification variables. For measurement effect, randomisation at baseline includes practice, duration of diabetes, HbA1c result from the practice record and patient baseline measure of self-report adherence. For intervention, randomisation at eight weeks includes the baseline measurement-effect randomisation group allocation, and baseline HbA1c is included instead of the practice record. Staff receiving and downloading the data from the electronic medication-monitoring device are blind to allocation, as are laboratory staff measuring HbA1c.

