#### Baseline measures to characterise participants

Socio-demographic and clinical measures include measures of duration of diabetes, overall drug regimen and numbers of prescribed medication doses. For the purposes of characterising the eligible population and randomisation at baseline, the last practice-recorded HbA1c is also recorded.

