### Sample size

The trial is planned to follow-up 200 patients, providing 80% power at the 5% significance level to detect a difference in means between randomised groups of 5% (1.5 days per month difference) in the percentage of days on which the correct number of doses is taken. This was based on an estimate of the standard deviation of this measure of 13.5% in a pilot study for the trial conducted in 2001 in Newmarket, Cambridgeshire (personal communication [name]). Assuming a follow-up rate of 85%, a maximum of 250 participants would need to be recruited.

For the measurement effect we can detect a difference of one point in the MARS self-reported adherence measure (a small to moderate effect size) [24], with 80% power and a two sided test at the 5% level with a conservative estimate of a 2.5% standard deviation. We will also detect a 0.5% difference in HbA1c at eight weeks with 80% power at the 5% level assuming a standard deviation of 1.25% for HbA1c.

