#### Sub-group analyses

Subgroup analyses will be carried out to explore the impact of number of medications, age, HbA1c, self-reported adherence at baseline and prior randomisation to the electronic medication-monitoring device on the intervention effect.

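### The primary comparison does not use the monitored drug's daily dose frequency, a baseline item that the protocol itself links to adherence, so avoidable variance stays in the estimate

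*Protocol article*

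**What the plan says.** All references are to the protocol article.

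- **Eligibility (Patients):** patients must be "currently taking any oral glucose-lowering agent and with a HbA1c ≥ 7.5"% or above. No limit is set on doses per day. Under Measurement effect, the monitored drug is metformin or, for patients not taking it, another oral agent.
- **Primary outcome (Abstract, Sample size, Analysis):** the percentage of days with the correct number of doses taken. The Measurement section words it slightly differently, as the prescribed dose of the main drug being taken as prescribed.
- **Background:** the protocol describes up to half of prescribed medication as possibly not taken as prescribed, "with adherence to medication falling as dosage frequency rises [6"].
- **Baseline measures:** these include "overall drug regimen and numbers of prescribed medication doses".
- **Randomisation:** the first minimisation uses practice, diabetes duration, practice-record HbA1c and self-reported adherence. For the main comparison, "randomisation at eight weeks includes the baseline measurement-effect randomisation group allocation, and baseline HbA1c is included instead of the practice record".
- **Sub-group analyses:** these will "explore the impact of number of medications, age, HbA1c, self-reported adherence at baseline" and prior allocation to the monitor.
- **Analysis, Intervention effect:** the group means are compared by a non-parametric bootstrap, with a 95% confidence interval. No covariate is named.
- **Analysis, Measurement effect:** continuous measures are adjusted for their own baseline value from before the first randomisation, where there is one.

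**The concern.** The outcome is an all-or-nothing score for each day. Two patients who take each single dose equally reliably will score differently if one has one dose a day to get right and the other has three. Dose frequency is therefore built into the outcome, and the protocol separately cites it as a driver of adherence. It is known before randomisation and is due to be collected in every participant, but the primary comparison makes no use of it.

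The one adjustment the article describes does not fill the gap. It uses the measure's own value from before the first randomisation. Monitor data cannot exist at that point: Table 1 shows the first readings at eight weeks, and only for half of the participants. Dose frequency is thus one of the few baseline variables that is available for everyone and tied directly to this outcome.

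What is at stake is precision. Variation between regimens stays in the residual, the interval is wider than it need be, and power is lower.

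**Working it through.** **1. The plan's own figure.** Inputs from Sample size: the number of patients, power and test level are stated as "The trial is planned to follow-up 200 patients, providing 80% power at the 5% significance level". The target is 5 percentage points of days. For the SD, the article gives this source: "estimate of the standard deviation of this measure of 13.5% in a pilot study". Allocation is 3:2 (Abstract), so about 120 v 80. The test is taken as two-sided, because sidedness is not stated for this outcome.

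- SE of the difference = 13.5 × √(1/120 + 1/80) = 13.5 × 0.1443 = 1.949.
- Power = Φ(5/1.949 − 1.96) = Φ(0.606) = 72.8%, not 80%.
- Control patients needed for 80% = (1.960 + 0.842)² × (13.5/5)² × (1 + 1/1.5) = 95.4, so 96 + 144 = 240 in total.
- A one-sided 5% test would need 190 in total.

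The shortfall is a separate matter. It is shown here because it sets the baseline for what adjustment could recover.

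**2. How dose frequency enters the outcome.** Assume each dose is taken correctly with probability p, the same for all patients and independent within a day. The expected percentage of correct days with k doses a day is then 100 × p^k. Assume a split of 25% once, 50% twice and 25% three times daily. Neither the split nor p is in the documents.

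Formulas:
- Between-regimen SD = weighted SD of the three expected percentages.
- R² = SD²/13.5². This takes the pilot SD to include the regimen variation.
- Adjusted SE = 1.949 × √(1 − R²).
- Power = Φ(5/SE − 1.96).

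| p | Correct days, k = 1 / 2 / 3 | Between-regimen SD | R² | Adjusted SE | SE reduction | Power at 200 |
|---|---|---|---|---|---|---|
| 0.97 | 97.0 / 94.1 / 91.3 | 2.03 | 0.023 | 1.926 | 1.1% | 73.7% |
| 0.95 | 95.0 / 90.3 / 85.7 | 3.28 | 0.059 | 1.890 | 3.0% | 75.3% |
| 0.90 | 90.0 / 81.0 / 72.9 | 6.05 | 0.201 | 1.742 | 10.6% | 81.9% |

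An R² of about 0.16 would be needed for 200 patients to give 80% power.

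**3. Chance imbalance is the same quantity, not a second harm.** One standard error of imbalance is SD × 0.1443, which is 0.29, 0.47 and 0.87 points for the three rows. At p = 0.90, √(1.949² − 0.873²) = 1.742, exactly the adjusted SE in the table. The two descriptions must not be added together.

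**4. Allocation or analysis?** A simulation of 6,000 runs per scenario used 200 patients at 3:2. A binary regimen group had assumed prevalence 50% and a 10-point outcome gap, so R² = 10² × 0.5 × 0.5/13.5² = 0.137.

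| Allocation | Power, unadjusted | Power, adjusted |
|---|---|---|
| Simple | 74% | 79% |
| Stratified on regimen | 75% | 80% |

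Stratifying without adjusting also made the test conservative (type I error about 3.5%). Nearly all the gain comes from the analysis.

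**The case against.** - **No trial balances on every predictor.** Leaving one out of the minimisation is a choice, not a contradiction, and covariates may be set in an analysis plan that is not shown. This stands in part: the article's silence is not an error. But it does state its primary comparison, and that comparison can be improved at negligible cost.
- **A reader might infer that balance is lost or the estimate biased.** The documents do not support that. Randomisation balances dose frequency in expectation. Self-reported adherence, which is a minimisation factor, may also absorb part of its effect.
- **A reader might infer that the remedy is another minimisation factor.** The simulation shows that this alone adds about one power point.
- **The size is assumed.** This stands. The Background describes intentional lapses. If a whole day's doses are skipped together, p^k overstates the gap between regimens, and with complete dependence the gap from this mechanism vanishes. The Background also notes that control-group adherence in such trials is often high, which points to the small end of the range.
- **A reader might infer that the subgroup list is wrong because it uses number of medications.** Number of medications measures total regimen burden, a legitimate exploratory question. Baseline self-reported adherence already addresses whether the intervention works where adherence is poor. Replacing one exploratory variable with another is preference.

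**Conclusion.** The point holds as a modest loss of precision. The protocol cites dose frequency as a determinant of adherence, scores the outcome in a way that depends on it and records dose numbers at baseline, but the stated primary comparison does not use it. There is no bias.

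Under the assumptions above, adjustment would cut the standard error by about 1% to 11%, worth roughly 1 to 9 power points at 200 patients. The true gain could be below that range if doses within a day are missed together, or if self-reported adherence already captures much of the effect. The documents cannot narrow the range further. The improvement is still worth making: it uses data already planned, and on its own inputs the trial has about 73% power at 3:2 with a two-sided test.

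**What to change.** In Analysis, Intervention effect, prespecify daily dose frequency of the monitored drug (once / twice / three or more) as a covariate in the primary comparison. One way is a regression-adjusted difference in means with a bootstrap confidence interval, which keeps the planned estimand and interval method. Include the same variable in the multiple-imputation model.

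Take the value from the baseline record and fix it before the eight-week randomisation. State in advance which drug counts as the monitored one for patients who are still in standard packaging at that point, so that the covariate cannot depend on allocation.

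Optional: add dose frequency to the eight-week minimisation if randomisation has not begun, or list it as an exploratory subgroup alongside number of medications, not in its place.

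The cost is one covariate with up to three levels. No new patients, visits or procedures are needed. The only check is that baseline dose numbers are recorded drug by drug, so that the monitored drug's frequency can be read off.
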